## Abstract

**Background:**

Osteoarthritis (OA) is a prevalent chronic disease and a leading cause of disability in adults. For people with knee and hip OA, symptoms (e.g., pain and fatigue) can interfere with mobility and physical activity. Whereas symptom management is a cornerstone of treatment for knee and hip OA, limited evidence exists for behavioral interventions delivered by rehabilitation professionals within the context of clinical care that address how symptoms affect participation in daily activities. Activity pacing, a strategy in which people learn to preplan rest breaks to avoid symptom exacerbations, has been effective as part of multi-component interventions, but hasn't been tested as a stand-alone intervention in OA or as a tailored treatment using accelerometers. In a pilot study, we found that participants who underwent a tailored activity pacing intervention had reduced fatigue interference with daily activities. We are now conducting a full-scale trial.

**Methods/Design:**

This paper provides a description of our methods and rationale for a trial that evaluates a tailored activity pacing intervention led by occupational therapists for adults with knee and hip OA. The intervention uses a wrist accelerometer worn during the baseline home monitoring period to glean recent symptom and physical activity patterns and to tailor activity pacing instruction based on how symptoms relate to physical activity. At 10 weeks and 6 months post baseline, we will examine the effectiveness of a tailored activity pacing intervention on fatigue, pain, and physical function compared to general activity pacing and usual care groups. We will also evaluate the effect of tailored activity pacing on physical activity (PA).

**Discussion:**

Managing OA symptoms during daily life activity performance can be challenging to people with knee and hip OA, yet few clinical interventions address this issue. The activity pacing intervention tested in this trial is designed to help people modulate their activity levels and reduce symptom flares caused by too much or too little activity. As a result of this trial, we will be able to determine if activity pacing is more effective than usual care, and among the intervention groups, if an individually tailored approach improves fatigue and pain more than a general activity pacing approach.

**Trial Registration:**

ClinicalTrials.gov: NCT01192516

## Background

Osteoarthritis (OA) is a prevalent and chronic disease. It affects over 27 million adults in the U.S. and is expected to increase as the population ages [1]. OA is more prevalent among females, however, male veterans are also significantly affected, with 1/3 of males of all ages diagnosed and nearly half of those who use the Veteran's Affairs (VA) healthcare system [2]. OA causes substantial physical and psychosocial disability. By 2020, it is expected that 12 million people in the U.S. will report activity limitations due to arthritis [3].

A primary reason people with OA seek treatment is for pain relief. Whereas people with OA often receive pharmacological treatment for pain reduction, non-pharmacological treatment for symptoms is considered the foundation of OA management [4,5]. Rehabilitation professionals, such as occupational therapists (OTs), can tailor non-pharmacological symptom management interventions so as to promote adherence and behavior change. To date, however OTs have had only limited involvement in tailoring such interventions for people with OA. More research is needed on the effectiveness of these tailored symptom management interventions when delivered by rehabilitation professionals within the context of clinical care. Well-established community-based programs on self-management strategies (such as the Arthritis Self-Management Program) have been shown to have small but positive effects on pain and arthritis self-efficacy [6-8]. Although community-based programs are an important tool for OA management, such programs do not optimize the use of rehabilitation professionals in the delivery or tailoring of these programs.

### Behavior Change and Tailoring Interventions

A tailored approach to interventions is being increasingly recommended in order to make the content personally relevant and to promote long-term behavior change. Several interventions are individually tailored on key variables identified in theoretical health behavior models, such as motivational readiness, decisional balance, or self-efficacy [9-11]. Interventions also have been tailored on personal characteristics (e.g., gender [12], depression [13], pain level [14]). There is growing evidence that tailoring enhances the effectiveness of clinical interventions designed to alter health risk behaviors such as smoking [15,16] and low physical activity [17,18].

For arthritis management interventions, Social Cognitive Theory has often been used as the theoretical foundation of intervention development [19,20]. It posits that people learn through an interaction of social and environmental influences that contribute to their own motivations and behaviors [21]. To adopt a new health behavior, the central determinants include 1) *knowledge *of the risks and benefits, 2) *outcome expectations *about costs and benefits for engaging in health behaviors, 3) the health *goals *people set for themselves and plans for goal achievement, 4) the *perceived facilitators and barriers *(such as external social or work demands), and 5) *self-efficacy*, the belief in the ability to perform under a certain set of conditions [21,22]. Self-efficacy is often a central focus in self-management interventions because it influences behavior both directly and indirectly through the other determinants above [22]. Numerous studies have found that improvements in pain coping skills are related to improvements in arthritis self-efficacy [19,23,24].

In this study, the intervention is designed to assist people in enhancing their arthritis self-efficacy by individually tailoring the use of activity pacing strategies to the context of where and when the strategies may be most useful. According to Social Cognitive Theory, self-efficacy is enhanced by building competency through practice (and by the rewards associated with success) in specific situations or conditions [22]. By tailoring activity pacing instruction to individuals' real-life routines and activities, there is a greater chance for learning to occur and for self-efficacy to be enhanced given the greater proximity of the pacing schedule to real-life and personally relevant activities.

### Pain, Fatigue, and Their Relationship to Physical Activity

Both pain and fatigue symptoms are linked to various functional problems in OA. Pain in OA affects the ability to engage in activities of daily living, work, and other meaningful activities and is associated with a reduced quality of life [25-27]. Fatigue is not as well-studied in OA, however, it is one of the most frequently reported OA symptoms [28,29]. Attention to the clinical importance of fatigue is growing. In large studies, substantial fatigue was reported by 41% of patients with OA [28], and problematic fatigue or tiredness was reported in moderate levels [30]. Fatigue in OA is one of the strongest predictors of functional disability [28,31] and work dysfunction [28]. Fatigue has also been associated with pain, sleep problems, functional disability, and depression [28,30-32]. Qualitative studies have further characterized the fatigue experience in OA as debilitating, causing activity restriction, and greatly impacting life [29,33].

A better understanding of how symptoms affect activity on a more micro level, such as over a day, week, or month, can help refine and tailor OA interventions. For example, tailored interventions may target *timing *of behaviors such as medication usage or variability in symptoms by time [34]. Although OA symptoms are believed to be less variable than other rheumatic conditions such as rheumatoid arthritis (RA), an emerging body of research has shown that there is important variability in OA pain [35-38] across days or even within a day. These pain fluctuations have been associated with limited daily activities, days of missed work, sleep interference, and mood [36], and increased pain variability may be associated with personal factors [e.g., body mass index (BMI)] [35].

Fewer studies have examined fatigue variability in OA. Given the strong relationship between pain and fatigue [28,31,32] in OA and other conditions, it is not surprising that fatigue is often considered a by-product of pain. However, when pain and fatigue are measured daily or within-day, differences emerge. For example, compared to samples of persons with RA and fibromyalgia, daily fatigue fluctuations were not as strongly associated with daily pain fluctuations in persons with OA [39]. In our work, we found that within-day fatigue was experienced at greater intensities than was pain [40]. Additionally, in one of the few studies to examine the symptom-activity relationship in OA, we found that fatigue was more highly associated with objective physical activity (PA; measured by accelerometer) compared to pain [40]. Lastly, we found differential effects for pain and fatigue by group when we tailored activity pacing [41], providing support for addressing pain and fatigue separately.

### Pacing Intervention Effectiveness

Although activity pacing is a recommended non-pharmacological intervention for OA management based on consensus guidelines [4], its effectiveness as a stand-alone intervention is understudied. Typically, activity pacing is combined with other programs (e.g., coping skills training, cognitive behavioral therapy). In these studies of knee or hip OA, the overall programs have been effective at reducing pain [23,24]; however, it is impossible to disentangle the unique effects of activity pacing. Due to differences in how activity pacing is understood as a strategy, there is variability in activity pacing instruction and its delivery by therapists [42,43]. This trial addresses these limitations by using a standardized approach to teaching activity pacing to adults with knee or hip OA. This approach is structured around the overall goal of activity pacing, which is the balance between activity and rest in order to accomplish necessary and valued activities [44]. In this study, we will also be able to examine the unique effects of tailored activity pacing on fatigue for knee or hip OA in which our preliminary results showed significant improvements in fatigue compared to a general activity pacing intervention [41]. The conceptual model that guided intervention development is shown in Figure 1.

**Figure 1 F1:**
[figure not shown]
**Model of Symptoms, Self-Efficacy, Physical Function and PA in Adults with Osteoarthritis**.

## Methods/Design

This is a three-arm randomized controlled trial that will examine outcomes at baseline, posttest (approximately 10 weeks post baseline), and 6 months. Ethical approval for this study was obtained by the University of Michigan Medical School Institutional Review Board and the Subcommittee on Human Studies in the Veteran's Affairs Ann Arbor Healthcare System. The overall goal of the study is to examine the effectiveness of a tailored activity pacing intervention for adults with symptomatic knee or hip OA. The primary outcomes are fatigue and pain.

The specific aims are:

Aim 1: To examine the effectiveness of a tailored activity pacing intervention on fatigue, pain, and physical function.

Aim 2: To determine if increased arthritis self-efficacy post intervention is related to improvements in symptom severity and function.

Aim 3: To evaluate the effect of tailored activity pacing on physical activity.

Eligible individuals are randomly stratified by age and gender into one of three arms: tailored activity pacing intervention, general activity pacing intervention, or usual care. The tailored and general activity pacing interventions are equivalent in session number and length. Participants are involved in study procedures over 6 months. For the intervention groups, involvement consists of 3 individual sessions, 3 testing visits, 3 home monitoring periods, 3 weekly follow-up phone calls, and monthly contact phone calls until the outcome assessment at 6 months. The usual care group participates in all activities described above except for the intervention sessions and the 3 weekly follow-up phone calls.

### Participant Recruitment

Community-living veteran and non-veteran participants are recruited from the University of Michigan and VA clinics, senior housing sites, and through public advertisements. Based on our previous studies, our optimal recruitment methods are ad placement at clinics and through community ads and fliers. As in our previous studies, areas with higher concentrations of minorities are particularly targeted for recruitment. Minorities such as African Americans are particularly important to include in this study because they not only have higher rates of knee and hip OA than Caucasians [45], they also report more severe OA symptoms and more physical disability even when controlling for demographics and other factors [46]. In addition, African Americans are less likely than Caucasians to opt for hip or knee replacements [47] and more likely to manage OA through home remedies that often have little to no evidence of effectiveness (such as copper bracelets or herbal medicines) [48].

### Eligibility Criteria

The following inclusion criteria were designed to identify a cohort of community-living adults who are likely experiencing symptoms specifically due to their OA. Prior to enrollment, each prospective participant is evaluated for inclusion. Table 1 lists the inclusion and exclusion criteria.

**Table 1 T1:** Eligibility Criteria

Inclusion Criteria
• Age ± 50 years old • Pain for at least 3 months duration • Mild to moderate severity on the WOMAC pain scale • Radiographic evidence of knee or hip OA • Community-living (i.e, own home, senior residence, apartment) • Adequate cognitive status (score of > 5 on the 6-Item Screener)[66] • Ambulatory either with or without an assistive device • Reliable operation of the Actiwatch-Score accelerometer • English-speaking

**Exclusion Criteria**

• Medical conditions that may interfere with pain and fatigue reporting or activity monitoring (multiple sclerosis, lupus, rheumatoid arthritis, Parkinson's disease, peripheral neuropathy) • Cancer diagnosis in the last year (other than skin cancer) or currently undergoing treatment for cancer • Medicine changes within last 2 weeks • Anemia or unmanaged thyroid dysfunction (from blood work result) • 2 or more days of complete bed rest within last month • Limb hemiplegia or amputation • Knee arthroscopic procedure within the last 2 months • Replacement of any hip or knee within the last 6 months • Knee joint injection within the last 3 months • Current receipt of physical or occupational therapy for OA symptoms or knee/hip problems • Current attendance or attendance in the past 12 months in a cognitive behavioral program or other self-management program that includes activity pacing instruction.

### Procedures

Figure 2 shows a flow chart of the study protocol. In brief, trained research personnel screen individuals for eligibility, administer performance-based assessments, and train participants in the use of the wrist-worn accelerometer and accompanying logbook. Participants provide written consent to participate in the study. They wear the accelerometer for a 7 day period and then return materials in person or by mail to the study team. Participants are randomly stratified by age and gender into the tailored activity pacing intervention, general activity pacing intervention, or usual care group. The usual care group participants undergo all outcome assessments and have maintained contact through monthly emails between outcome assessments similar to the intervention groups. The contact period between Weeks 11 - 23 is being undertaken to better ensure participation in the 6 month assessment for all groups. Each intervention arm involves 3 individual sessions with an OT. In the tailored activity pacing group, data collected from the home monitoring period are used to generate reports for participants about how symptoms relate to physical activity and are used by the occupational therapist. The general activity pacing group does not use the information from the home monitoring period during OT sessions.

**Figure 2 F2:**
[figure not shown]
**Study Flow Chart**.

### Study Arms

#### Usual Care Group

This group participates in all outcome measures and monthly outcomes are tracked during the study period using a survey measure to determine if any new OA pharmacological or non-pharmacological treatments are undertaken (e.g., injection, physical therapy, medication change) to treat symptoms.

### General and Tailored Activity Pacing Interventions

Regardless of whether people are assigned to the tailored activity pacing or general activity pacing intervention groups, participants meet with an OT for 3 individual sessions (total treatment time: 3 hours over Weeks 4 - 9 of the study). The first session for both the tailored activity pacing and general activity pacing includes a brief presentation by the OT on the nature of OA and how physical demand and mood can affect the symptom experience. This is followed by group-specific instruction on activity pacing as a tool for symptom management which includes printed materials that are a take-home reference for the participant. In the tailored activity pacing intervention, the OT discusses how to incorporate activity pacing based on the individual's profile of symptoms and activities determined from the baseline home monitoring period. In the general activity pacing intervention, the OT uses generic examples and does not mention the individual symptom experience from the baseline home monitoring period. By the end of the first OT session for both the tailored and general activity pacing groups, the participants develop a time-based activity plan with goals related to activity pacing. The second session focuses on individual progress with activity pacing, goal setting, and addressing barriers to using the recommended strategies. The third session focuses on reviewing activity pacing tenets, evaluating the use of time based activity pacing and planning for the future. After the 3 individual sessions have concluded, the OT makes 3 brief follow-up phone calls (1 call per week) to discuss activity pacing progress, symptoms, and any barriers.

### Strategies for Ensuring Treatment Fidelity

Treatment fidelity is defined as "the procedures used to monitor and enhance the reliability and validity of behavioral interventions [49]," and is an essential component of this study. Per recommendations from the National Institutes of Health (NIH) behavior change consortium [49,50], several strategies are being used to ensure treatment fidelity in this study. These strategies target fidelity of treatment delivery (standardized modules for the intervention and interventionist training and monitoring) and treatment receipt (i.e., participant involvement in treatment).

### Fidelity of Treatment Delivery

We have designed the study such that both intervention groups are equivalent in dose and administration of treatment (i.e., the number and length of sessions), including the manner in which participants are contacted from 10 weeks through 6 months. There are several procedures in place to ensure fidelity in how treatment is delivered. It is likely that there will be multiple therapists per active intervention arm (i.e., tailored activity pacing and general activity pacing). We decided that extra therapists per group could reduce the possibility of treatment effect due to therapist characteristics and ensure that we can deliver the intervention in the event that any interventionists drop out of the study. All therapists will undergo an initial training period which will involve structured education via a manual and a series of didactic sessions with the principal investigator (PI) and study team members. The initial training will also involve role playing in pairs and an observer who will rate the mock treatment session for key concepts to ensure consistency across therapists. Any discrepancies in how the intervention is delivered across therapists will be discussed and a consensus will be reached about intervention delivery.

To assess therapist adherence to the intervention protocol, they are asked to log the actual treatment time per session with each individual. The therapist also has a checklist of items for each visit to facilitate consistent presentation of the protocol. In addition, we are audiotaping sessions (as long as each individual consents to that process) and an independent rater listens to the tapes shortly after the sessions to determine if original criteria for intervention delivery in each treatment arm are being met. Any discrepancies in the audiotapes by therapists in a particular treatment arm will be resolved in a face-to-face meeting through consensus to reduce any variability in delivery. To prevent protocol 'drift', the PI and therapists in each arm have monthly telephone contact to discuss any issues and additional training sessions among therapists occurs as needed.

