### Data Analysis

The target sample size in this study is 156 participants. In our recruitment plans, we have factored in a 30% attrition rate to achieve this number. Although there are three arms to the study: tailored activity pacing, general activity pacing, and usual care group, the study was powered to find effects between the two active intervention groups (tailored activity pacing and general activity pacing). Specifically, the power analysis was based on our pilot data in which we compared the tailored activity pacing intervention with the general activity pacing intervention and detected large group differences using the effect size Cohen's d [65] on BFI fatigue severity and interference (d = .79 and 1.1 respectively) at 10 week-follow-up. Based on a 2 group t-test at a significance level of p = .05, we will have greater than 90% power to detect an effect size of .74 or larger with 40 people in each of the two active intervention groups. Because most people with OA do not receive this type of intervention, it is important to compare the active intervention groups to a group receiving usual care. The study was powered to detect treatment effects between the active intervention groups; therefore we will also have sufficient power to detect differences between the active intervention groups and usual care group.

To examine the effectiveness of a tailored activity pacing intervention on fatigue, pain, and physical function, we will use repeated measures analysis of variance (RM ANOVA) models to analyze the responses (pain, fatigue, and 6 minute walk test) at baseline, 10 weeks, and 6 months for the three treatment groups (tailored activity pacing, general activity pacing, and usual care group). This will allow us to estimate the effects of treatment group, time point and the treatment × time interaction. Similarly, we will use RM ANOVA models to determine if increased arthritis self-efficacy post intervention is related to improvements in symptom severity and function and to evaluate the effect of tailored activity pacing on physical activity.

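### The stated power and the repeated measures ANOVA treat participants as independent; if therapists are nested in arm and the therapist ICC is above 0, the tailored-versus-general comparison is less precise than planned and its test can exceed 5%

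*Protocol article*

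**What the plan says.** The Fidelity of Treatment Delivery section of the protocol article expects more than one therapist in each active arm: "It is likely that there will be multiple therapists per active intervention arm (i.e., tailored activity pacing and general activity pacing". The reason given is that "extra therapists per group could reduce the possibility of treatment effect due to therapist characteristics", together with cover in case a therapist leaves. The section speaks of therapists as belonging to an arm, but never states that a therapist treats in one arm only. It also lists manual-based training, observed role play, a checklist for each visit, logged treatment time, audiotapes reviewed by an independent rater, consensus meetings and monthly contact to prevent drift.

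Delivery is individual. Each active-arm participant has three sessions with an occupational therapist and then three phone calls. Usual care has neither.

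On the statistics, the Data Analysis section says that "the study was powered to find effects between the two active intervention groups". The calculation assumes a t-test between two arms of 40 at the 5% level and concludes: "we will have greater than 90% power to detect an effect size of .74 or larger". The analysis is a repeated measures ANOVA with treatment group, time and their interaction. No therapist term, ICC or design effect appears in the article.

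**The concern.** Participants treated by the same therapist may have more similar outcomes than participants treated by different therapists. If each therapist works in one arm, this shared component does not cancel in the tailored-versus-general difference. It adds variance to each arm mean, and a participant-level standard error does not see it.

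Using more therapists lowers that variance. Training and monitoring may lower the ICC. Neither makes a standard error that assumes independence correct while the ICC stays above 0. The repeated measures structure does not help, because therapist effects arise after baseline and so enter the group-by-time term.

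This is the comparison for which the trial was powered. With few therapists per arm, an apparent benefit of tailoring would partly reflect who delivered it. The interval would be too narrow and the power overstated.

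**Working it through.** **Inputs from the article:** significance level .05 (sidedness not stated; two-sided assumed), d = .74, 40 per active arm, total target 156 (156/3 = 52 per arm if equal).

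**Assumed, because the article gives no value:** 2 or 4 therapists per arm with equal caseloads; ICC of .01, .02 or .05; therapists nested in arm.

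**Step 1. The stated power.** The noncentral t with 40 independent participants per arm and d = .74 gives 90.5% two-sided (94.9% one-sided). The claim of more than 90% therefore reproduces with ICC = 0. The margin is thin: the smallest effect with 90% power at 40 per arm is d = .734.

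**Step 2. Clustering, 40 per arm.**
- Caseload m = 40 / therapists per arm, so m = 10 or 20.
- Design effect DE = 1 + (m − 1) × ICC. Example: 1 + 19 × .05 = 1.95.
- Effective n per arm = 40 / DE. Example: 40 / 1.95 = 20.5.
- Power: t-test at the effective n.
- Type I error of the unadjusted test = 2 × [1 − Φ(1.96 / √DE)].

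| Therapists per arm | ICC | DE | Effective n | Power at d = .74 | Type I error |
|---|---|---|---|---|---|
| 4 | .01 | 1.09 | 36.7 | 87.8% | 6.1% |
| 4 | .02 | 1.18 | 33.9 | 85.1% | 7.1% |
| 4 | .05 | 1.45 | 27.6 | 77.0% | 10.4% |
| 2 | .01 | 1.19 | 33.6 | 84.8% | 7.2% |
| 2 | .02 | 1.38 | 29.0 | 79.1% | 9.5% |
| 2 | .05 | 1.95 | 20.5 | 63.7% | 16.0% |

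Simulating the unadjusted t-test (40,000 trials per scenario) gave type I errors of 6.0, 7.0 and 10.5% with 4 therapists and 7.1, 9.4 and 16.2% with 2. Even without adjustment, that is, with the inflated error rate, the simulated rejection rate at d = .74 was below 90% in all six scenarios: 89.3, 88.6 and 86.4% with 4 therapists; 88.7, 87.0 and 83.0% with 2.

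**Step 3. If 52 per arm are analysed** (m = 13 or 26). Power without clustering is 96.2%.

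| Therapists per arm | ICC | DE | Power at d = .74 | Type I error |
|---|---|---|---|---|
| 4 | .01 | 1.12 | 94.2% | 6.4% |
| 4 | .02 | 1.24 | 91.8% | 7.8% |
| 4 | .05 | 1.60 | 83.6% | 12.1% |
| 2 | .01 | 1.25 | 91.5% | 8.0% |
| 2 | .02 | 1.50 | 85.9% | 11.0% |
| 2 | .05 | 2.25 | 69.2% | 19.1% |

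**Step 4. Therapists crossed with arm, shared main effect only.** With 4 therapists and 40 per arm, the simulated type I error is 4.9% at ICC .02 and 4.5% at ICC .05, so the unadjusted test is slightly conservative.

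**Step 5. Price of a full adjustment.** A test on therapist means has 2k − 2 degrees of freedom for k therapists per arm: 6 for k = 4 and 2 for k = 2. Its simulated power at ICC .01, .02 and .05 is 75, 72 and 63% for k = 4, and 40, 36 and 27% for k = 2.

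**The case against.** Only a condensed article is at hand. The full protocol or the SAP may add a therapist term, and naming group, time and their interaction does not exclude one. That stands as far as the final model goes. It does not rescue the power statement, which is a finished calculation and holds only without clustering.

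A reader might infer that the standard errors are definitely too small. The article does not support that. More than one therapist per arm is called likely, not certain; arm-specific therapists are implied, not stated; and no ICC is given. With crossed therapists the direction can reverse (step 4).

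A reader might also infer that extra therapists are the only safeguard. They are not: training, checklists and audiotape review all aim at uniform delivery and may hold the ICC down.

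The sample size matters too. The article says "The target sample size in this study is 156 participants" and "we have factored in a 30% attrition rate to achieve this number", which can be read as 156 after attrition. At 52 per arm, power stays above 90% at ICC .01 with either number of therapists, and at .02 with 4. This softens the loss of power but leaves the type I error above 5% under nesting.

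Finally, a therapist random effect as the primary model would be fragile with 2 therapists per arm. That stands and shapes the fix.

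**Conclusion.** The point holds conditionally. The article names a possible therapist effect, then states a power and model terms that take participants as independent. If therapists are nested in arm, the ICC is above 0 and no adjustment is made elsewhere, the tailored-versus-general test is anti-conservative. The stated power above 90% with 40 per arm is then missed even at an ICC of .01: 88% with 4 therapists per arm and 85% with 2. Across ICCs of .01 to .05, the type I error is about 6 to 10% with 4 therapists and 7 to 16% with 2. These sizes rest on assumed ICCs and therapist numbers. They show how sensitive the comparison is and do not estimate this trial's actual error rate.

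**What to change.** - Record each participant's treating therapist, and state how many therapists there are and whether they are nested in or crossed with arm. Therapists already log treatment time for each individual, so the link may already exist.
- Pre-specify a partially nested mixed model, with a therapist random effect in the two active arms only and a small-sample degrees-of-freedom correction such as Kenward-Roger. Use it as a sensitivity analysis beside the primary result, and as the primary model only if there are enough therapists per arm. If therapists are crossed, adapt the therapist term to that design.
- Report the therapist ICC with its interval.
- State that the power above 90% assumes no therapist clustering, and give power over a range of ICCs and for the number of participants expected to be analysed.

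The cost is one recorded variable, one added analysis and a few sentences. The downside is wider intervals. With only 2 therapists per arm there are about 2 degrees of freedom and the ICC can hardly be estimated, so the adjusted result would then mainly show how little can be said about therapist effects.
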